### Randomization and Allocation

Randomization of participants will be performed 1:1 into arbaclofen vs. placebo by a randomization website (Interactive Web Response System—IWRS) developed by the Data Management Department of the Julius Center, University Medical Center Utrecht (UMCU). Allocation will be sent to an unblinded dedicated pharmacist at each individual site as specified in a separate Pharmacy Manual. A central unblinded monitor will double check dispensation regularly. The rest of the study members are blind to allocation. Randomization will be stratified by site and age group (5–11 years old; 12–17 years old). Unblinding will only happen if the information can help treat an adverse event and for safety reasons.

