### Sample Size

Based on Veenstra-VanderWeele et al. (23), for a 5.3 (standard deviation of 15) change from weeks 0 to 16 in scores on the VABS−3 Socialization domain for those treated with arbaclofen vs. placebo, 100 participants are needed in each arm, assuming 2-sided testing at a significant level of 5 and 80% power. Allowing for 10% attrition, the total sample required would be 220, 110 in each treatment arm. Therefore, the sample from this study will be combined with that of the Canadian ARBA trial to attempt to answer to the key objective. AIMS-CT1 will recruit 130 participants across the seven study sites (i.e., ~19 participants each) and ARBA-Brain Canada will recruit 90 participants.

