### Statistical Analysis

Analysis will be performed both with an Intent to Treat (ITT) and as Per Protocol (PP) approach. The initial efficacy analysis will use the ITT sample, which includes all participants randomized who have at least one dose of medication and one post-baseline assessment. To be included in the PP sample, participants will fulfill ITT criteria and have attended at least 80% of the visits, have taken at least 70% of the prescribed medication and have a consistent pre- and post-intervention VABS−3 clinician rater.

Efficacy will be indicated by a difference between treatment arms at week 16, using Analysis of Covariance (ANCOVA; with follow-up score used as the dependent variable and treatment group as a factor) or logistic regression, and Chi-Square techniques, as appropriate. Age will be adjusted for and baseline scores will be used as covariates. Hypothesis testing will be performed at the 5% level of significance for 2-sided tests. Safety analyses will be conducted on all participants taking at least one dose of study medication by calculating the incidence of adverse events in each arm and summarizing laboratory and ECG assessments, physical examinations and vital signs.

A secondary analysis will be conducted by combining data from AIMS-CT1 and the ARBA Study to ensure statistical power for the assessment of efficacy of the primary outcome variable. Additional analyses will consider variables or sub-variables that will be different from or derivative of the primary and secondary hypotheses. Another level of analysis will look at data of individual sites. Power calculation was made for the primary outcome (VABS-3 social function domain), which justifies the a priori planned combination of the data of this study with that of ARBA Study in Canada. Other results will be considered secondary results and therefore more exploratory and hypotheses-generating.

While no interim analysis is planned, if necessary, the Data Monitoring Committee (DMC) will consider it and inform the Sponsor whether premature termination criteria are met.

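### Randomisation is stratified by site, but the stated efficacy ANCOVA leaves site out; adding it costs almost nothing, and the individual-site results should be labelled descriptive

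*Protocol article*

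**What the plan says.** In the Protocol article, Randomization and Allocation: "Randomization will be stratified by site and age group", the age bands being 5–11 and 12–17 years.

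Statistical Analysis gives the efficacy model as an ANCOVA of the follow-up score with treatment group as a factor, and adds: "Age will be adjusted for and baseline scores will be used as covariates". Site is not mentioned as a model term.

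The same section plans a site-level look at the data: "Another level of analysis will look at data of individual sites". It gives no aim, method or test for this. It then says of everything beyond the primary outcome: "Other results will be considered secondary results and therefore more exploratory and hypotheses-generating".

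Trial Design and Sample Size give 130 participants at seven sites in Spain, the UK and France, about 19 per site, with a target difference of 5.3 points and an SD of 15.

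**The concern.** The design uses two stratification factors, and the stated model carries only one of them (age) into the analysis. Stratifying by site balances the arms within each site. If site also predicts the outcome, a model without site leaves the between-site variation in the residual. The treatment estimate itself is hardly affected by that variation, because the arms are balanced on it, but its standard error is inflated. The test then rejects too rarely, and precision that the stratification had secured is lost.

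Site differences are plausible here. The primary outcome is an interview with a parent, held in several languages by different interviewers. The Discussion acknowledges the difficulty of multilingual administration, and pandemic adaptations followed local rules. Precision also matters, because the Sample Size section asks for 220 participants and this trial recruits 130.

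The site-level look raises a related question: what can about 19 participants per site show?

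**Working it through.** **1. Model terms against design factors**

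| Factor | Used in randomisation | Named in ANCOVA |
|---|---|---|
| Age group | yes | yes, as age |
| Site (7) | yes | no |
| Baseline score | no | yes |

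**2. Size of the effect of omitting site**

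The between-site share *s* of residual variance, after baseline and age, is not in the article. It is assumed at 0%, 5%, 10% and 20%.

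As a guide, the standard error without site exceeds that with site by a factor of at most about 1/√(1 − s): 1.026 at 5%, 1.054 at 10% and 1.118 at 20%. With only seven sites the realised factor is a little lower, so it was simulated under two sets of assumptions. Both use seven sites, two age groups, permuted blocks within strata and a true effect of 5.3 for power.

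- Setting A: N = 130, SD 15, baseline correlation 0.6 (assumed), so residual SD = 15 × √(1 − 0.36) = 12; 2,500 trials per setting.
- Setting B: N = 126 (9 per stratum, blocks of 4), residual SD 15; 6,000 trials under the null and 3,000 at 5.3.

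| Site share | A: mean SE without / with site | Ratio | B: 95% CI half-width without / with site | Ratio |
|---|---|---|---|---|
| 0% | 2.107 / 2.112 | 1.00 | 5.296 / 5.312 | 1.00 |
| 5% | 2.106 / 2.063 | 1.02 | 5.290 / 5.187 | 1.02 |
| 10% | 2.099 / 2.010 | 1.04 | 5.268 / 5.046 | 1.04 |
| 20% | 2.075 / 1.886 | 1.10 | 5.232 / 4.750 | 1.10 |

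| Site share | Type I error without site, A / B | Power without → with site, A | Power without → with site, B |
|---|---|---|---|
| 5% | 4.6% / 4.7% | 71% → 73% | 50.4% → 51.9% |
| 10% | 3.9% / 4.1% | 71% → 74% | 49.6% → 52.5% |
| 20% | 3.3% / 3.5% | 71% → 78% | 51.6% → 59.5% |

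With site in the model, type I error in setting B is 5.0% at each of these shares. With no site effect, including site costs 2.112/2.107 − 1 = 0.2% in standard error (A) and 5.312/5.296 − 1 = 0.3% in half-width (B).

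The two settings differ in absolute power because their residual SDs differ (12 against 15). They agree on the ratios and closely on the gains.

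**3. Precision of a single site**

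- The plan's own figure: 130/7 = 18.6, which reproduces its stated value of about 19. Per arm this is 130/14 = 9.29.
- Without baseline adjustment: SE = 15 × √(2/9.29) = 6.96; half-width = 2.11 × 6.96 = 14.7 points.
- With an assumed baseline correlation of 0.6: SE = 12 × √(2/9.29) = 5.57; half-width = 2.12 × 5.57 = 11.8 points.
- Power at one site for a 5.3-point effect is 11–12% unadjusted, and about 14% to 19% for assumed baseline correlations of 0.5 to 0.7.
- Chance that one site shows the wrong sign when the true effect is 5.3: Φ(−5.3/6.96) = 22% unadjusted.

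**The case against.** The strongest reply is that the loss may be close to nil. The article reports no between-site variance, and its own safeguards point to the low end of the range. Table 2 requires 90% reliability with a gold standard rater, regular reliability meetings across sites, and the same interviewer and informant at both timepoints. The Discussion adds training across sites and review of at least a quarter of the recordings. With the same rater at both visits, the baseline covariate absorbs part of any stable site or rater offset. This stands, and it limits the size of the point. It does not remove it: drift after baseline need not be absorbed, and adding site costs almost nothing if the safeguards work.

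A second reply is that a statistical analysis plan, not shown here, could add site. That is possible. But the article names its covariates, and the list does not match its own randomisation.

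A reader might also infer more than the article supports:

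- That the intervals are certainly too wide. This depends on an unknown site share and could be 0%.
- That the primary test is at risk of a false positive. The error runs the other way.
- That site results will be tested one by one. Seven independent 5% tests would give 1 − 0.95⁷ = 30% chance of at least one false positive, but no such tests are planned. The general rule, "Hypothesis testing will be performed at the 5% level of significance for 2-sided tests", is not tied to sites, and results beyond the primary outcome are called exploratory. Nor are site summaries worthless: they are imprecise, but harmless as a consistency check.
- That the combined analysis with the Canadian trial wrongly lacks a trial term. The article states no model for that analysis, so there is nothing in it to correct.

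**Conclusion.** The mismatch is real: one of two stratification factors is missing from the stated model. Its consequence is modest and conditional. Over assumed site shares of 0% to 20% the standard error is 0% to about 10% too large, and 2% or less for shares up to 5%. The power gain from adding site is about 2 to 3 points at shares of 5% to 10% and 7 to 8 points at 20%. The absolute power levels above belong to the assumed scenarios and ignore the 10% attrition; they are not properties of this trial.

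The site-level analyses cannot support inference on a 5.3-point effect, with half-widths of about 12 to 15 points. The article does not claim that they will, so the need there is for a clear label. Overall severity is low to moderate.

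**What to change.** State the primary model as week-16 score on treatment, baseline score, age and site. If some sites turn out very small, pool them or use country, by a rule set before unblinding. The cost is one sentence and six degrees of freedom (seven sites minus one): with 130 analysed, residual degrees of freedom fall from 130 − 4 = 126 to 120.

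For the individual-site results, say that they are descriptive: for example, a forest plot of site estimates with intervals and no site p-values, with a single treatment-by-site heterogeneity check. That is a second sentence and needs no extra data.

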## Abstract

**Background:** Autism Spectrum Disorder (ASD or autism) is characterized by difficulties in social communication and interaction, which negatively impact on individuals and their families' quality of life. Currently no pharmacological interventions have been shown to be effective for improving social communication in autism. Previous trials have indicated the potential of arbaclofen for improving social function among autistic children and adolescents with fluent speech. The AIMS2TRIALS-Clinical Trial 1 (AIMS-CT1) will examine whether arbaclofen is superior to placebo in improving social function and other secondary outcomes over 16 weeks, along with safety and tolerability profiles.

**Methods:** AIMS-CT1 is an international, multi-site, double-blind, parallel group Phase II randomized clinical trial. It will include 130 males and females aged 5:0–17:11 years, with a diagnosis of ASD and fluent speech. Eligible participants will be randomized on a ratio of 1:1 for a 16-week treatment period. Medication will be titrated over 5 weeks. The primary outcome is the effect on social function from weeks 0 to 16 measured on the Socialization domain of the Vineland Adaptive Behavior Scales, 3rd edition^TM^. Secondary outcome measures include the CGI–S (Clinical Global Impression–Severity), CGI–I (Clinical Global Impression–Improvement), other areas of adaptive function, social communication and other autism symptoms, co-occurring behavior problems and health-related quality of life. Genetic and electrophysiological markers will be examined as potential stratifiers for treatment response. Exploratory novel digital technologies will also be used to measure change, examining simultaneously the validity of digital biomarkers in natural environments. The safety and tolerability of the drug will also be examined. Our protocol is very closely aligned with a parallel Canadian trial of 90 participants (ARBA Study, US NCT number: NCT03887676) to allow for secondary combined analyses. Outcomes will be compared using both an Intent-to-reat and Per Protocol approach.

**Discussion:** The outcomes of this trial, combined with the parallel Canadian trial, will contribute to the evidence base for medications used to help social difficulties among young autistic individuals; demonstrate the capabilities of the AIMS-2-TRIALS network of academic centers to deliver clinical trials; and support future drug development.

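### The 80% power belongs to a pooled two-trial analysis that the article labels secondary; if AIMS-CT1 alone (N=130) is the primary test, its power is about 47 to 52% unadjusted on the stated inputs

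*Protocol article*

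**What the plan says.** The Objectives section assigns the primary objective, VABS-3 Socialization on arbaclofen against placebo, to AIMS-CT1.

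The Sample Size section plans "for a 5.3 (standard deviation of 15) change from weeks 0 to 16 in scores on the" Vineland socialization scale, "assuming 2-sided testing at a significant level of 5 and 80% power", and concludes that "100 participants are needed in each arm". It continues: "Allowing for 10% attrition, the total sample required would be 220, 110 in each treatment arm". Because one trial will not supply that number, "the sample from this study will be combined with that of the Canadian ARBA trial to attempt to answer to the key objective". The contributions are then split: "AIMS-CT1 will recruit 130 participants across the seven study sites", and the Canadian ARBA trial will recruit 90.

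The Statistical Analysis section sets an ANCOVA of the week-16 score, adjusted for age and baseline, with all tests at two-sided 5%. On pooling it says: "A secondary analysis will be conducted by combining data from AIMS-CT1 and the ARBA Study to ensure statistical power for the assessment of efficacy". The efficacy meant there is efficacy on the primary endpoint. It adds that the power calculation justifies the combination as planned in advance, and that other results are exploratory. The Abstract describes the alignment with the Canadian trial as being "to allow for secondary combined analyses".

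The article gives no power for AIMS-CT1 alone.

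**The concern.** One analysis has two roles. The Sample Size section makes pooling the means of answering the main question. The Abstract and the Statistical Analysis section make it secondary, which leaves the stand-alone AIMS-CT1 comparison as the primary test. The only sample-size justification in the article then supports the analysis that is not primary.

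Two things are at stake. A null AIMS-CT1 result would say little if its power against the planned effect is near one half. And if the stand-alone and pooled results disagree, the article does not say which one carries the efficacy conclusion, so the choice could be made after both are known.

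**Working it through.** **Inputs (Sample Size section).** Difference 5.3; SD 15; two-sided 5%; target power 80%; 100 per arm before attrition; 10% attrition; 220 in total; AIMS-CT1 130, ARBA 90. Allocation in AIMS-CT1 is 1:1; the same is assumed for ARBA. Standardised difference: 5.3/15 = 0.353.

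**1. The article's own figure.** n per arm = 2 × [15 × (1.960 + 0.842)/5.3]² = 125.7, so 126 (127 by t-test). The stated 100 does not reproduce. Variants:
- One-sided 5%: 2 × [15 × (1.645 + 0.842)/5.3]² = 99.04, so 100. This matches the stated number but not the stated two-sided test.
- Two-sided 5% with 100 per arm and a difference of 5.3 needs an SD of about 13.4. As a residual SD after baseline adjustment, that means √(1 − r²) = 13.4/15, so r is about 0.45. The article states neither.
- Attrition: 200 × 1.1 = 220, or 200/0.9 = 222.2, so 223. The step from 200 to 220 is close enough.

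**2. AIMS-CT1 alone, unadjusted (two-sample t-test).**
- After 10% attrition: 130 × 0.9/2 = 58.5 per arm. Noncentrality 0.353 × √(58.5/2) = 1.91; power 47%.
- No attrition: 65 per arm. Noncentrality 0.353 × √(65/2) = 2.01; power 52%.
- Difference detectable with 80% power at 58.5 per arm: about 7.8 points, against 5.3 planned.

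**3. AIMS-CT1 alone, taking 100 per arm for 80% at face value.** The noncentrality at 100 per arm is then 1.960 + 0.842 = 2.802, and it scales with √(n/100):
- 58.5 per arm: Φ(2.802 × √0.585 − 1.960) = 57%.
- 65 per arm: Φ(2.802 × √0.65 − 1.960) = 62%.

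**4. AIMS-CT1 alone with baseline adjustment.** If SD 15 describes scores rather than change, ANCOVA reduces it to 15 × √(1 − r²). The article gives no r, so these values are assumptions. Power is for 58.5 per arm, by t-test:

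| Assumed r | Residual SD | Power |
|---|---|---|
| 0.3 | 14.3 | 51% |
| 0.5 | 13.0 | 59% |
| 0.7 | 10.7 | 76% |

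**5. Pooled analysis, unadjusted.** After attrition, 220 × 0.9/2 = 99 per arm: power 70%. With all 110 per arm: 74%. For 80%, 127 per arm are needed, or 254/0.9 = 282.2, about 283 randomised. With an assumed r of 0.5, the pooled analysis has about 81% at 99 per arm.

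**6. Two tests of one hypothesis.** The stand-alone and pooled statistics share the AIMS-CT1 data, so their correlation is √(130/220) = 0.77. For a bivariate normal with this correlation, the chance that at least one exceeds 1.96 in absolute value under the null is 8.0% (9.75% if they were independent). This applies only if either test may support an efficacy claim.

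**The case against.** The shortfall is not hidden. The article says that more participants are needed than AIMS-CT1 will recruit, that pooling is there for power, and that it was planned in advance. This is a Phase II trial, and a pooled secondary analysis is legitimate. That stands, and it limits the defect to an unclear designation and an incomplete power statement. It does not remove the conflict between sections over which analysis is decisive.

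The 47% comes from an unadjusted comparison, while the planned analysis is an ANCOVA with baseline as covariate, and it is unclear whether SD 15 refers to scores or to change. This also stands, so the power is given as a range. At an assumed r of 0.7, AIMS-CT1 alone comes close to 80%; at 0.5 or below it does not.

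A reader might infer that the trial grants itself two unadjusted chances of success and so carries an 8% false-positive rate. The documents do not support that. No section says that either test may establish efficacy. If pooling is secondary, a positive pooled result does not rescue a failed primary; if pooling answers the key objective, the stand-alone test is not a separate route. The 8% needs both readings at once. Test order and alpha handling may also be set in a SAP that is not shown.

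A SAP could supply model terms and an order of testing. It would not make the article's sections agree on the role of pooling.

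**Conclusion.** The point holds as an inconsistency with a consequence for power. The Sample Size section uses the pooled sample for the key objective; the Abstract and Statistical Analysis sections rank pooling as secondary; the Objectives place the primary objective in AIMS-CT1.

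If AIMS-CT1 alone is primary, the stated 80% is not its power. On the stated inputs it is about 47 to 52% unadjusted, or 57 to 62% on the article's own sizing. With baseline adjustment it is 51 to 76% after attrition, under assumed correlations of 0.3 to 0.7 and SD 15 read as an SD of scores. If the pooled analysis is primary, power is about 70 to 74% unadjusted, and the stated 80% needs either an SD near 13.4 or a baseline correlation near 0.45 that the article does not give.

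An inflated error rate of about 8% is conditional on a decision rule that the article does not contain, and is not part of the conclusion.

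**What to change.** Before either trial is unblinded, name one confirmatory analysis of VABS-3 Socialization in the Statistical Analysis section, and make the Abstract, Objectives and Sample Size sections agree with it. Two choices resolve the conflict:

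- **Pooled analysis confirmatory.** The sizing points this way. Specify one ANCOVA on both trials, stratified by trial, at two-sided 5%, and report AIMS-CT1 alone as an estimate with a 95% CI and no separate efficacy claim. The cost is that the efficacy conclusion waits for the Canadian database lock and depends on a separate trial being completed.
- **AIMS-CT1 confirmatory.** State its limited power beside N=130 and declare the pooled result non-confirmatory. This costs wording only, but the weak power of the primary test remains.

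In either case, restate power in the Sample Size section for both analyses from a single calculation: about 47 to 52% for AIMS-CT1 alone and about 70 to 74% pooled, unadjusted. Then either correct the 100 per arm (about 127 on the stated inputs) or state the SD or baseline correlation that justifies it, and say whether SD 15 is for scores or for change. Printing the AIMS-CT1 figure beside an uncorrected 80% would mix two calculations. Restating power adds no participants; reaching 80% unadjusted on the stated inputs would take about 283 in total instead of 220.

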### Adverse Event Reporting

A medical history and physical examination will be conducted at screening to assist with interpretation of any adverse events (AEs), whether serious (SAEs) or non-serious, that occur during participation in the trial. The standard definition of AEs and SAEs will apply. In addition, pregnancy (in participant, or female partners of male participants), overdose (either accidental or intentional), cancer, potential drug-induced liver injury and suspected transmission of an infectious agent will be recorded as SAEs and follow these reporting regulations. In all cases of pregnancy, the treatment will be permanently discontinued in an appropriate manner and follow-up information on the course of pregnancy should be recorded if permission is given by the participant.

AEs and SAEs may be reported by the participant and/or their parent or found through medical examination or laboratory testing during phone call monitoring or face-to-face visits. The nature of each event, onset, duration and severity will be established and recorded, regardless of whether the event is related to the study treatment or not. AEs will be recorded from the initiation of study treatment until the final visit. All SAEs that occur between screening and up until 30 days of the last dose of the study treatment will be recorded. All AEs and SAEs will be followed-up proactively at subsequent visits/phone calls until either resolution, the condition stabilizes, the event is otherwise explained, or the participant is lost to follow-up. Follow-up is also required for AEs that cause interruption or discontinuation of the study treatment.

Usual convention will be used for reporting all AEs and SAEs following local laws and regulations. All SAEs will be reported to the sponsor and sponsor delegate within 24 h of the study site becoming aware of the event. Any Suspected, Unexpected Serious Adverse Reactions (SUSARs) will be reported to the appropriate regulatory authorities following local and global guidelines and requirements.

